## 1. Introduction

Secondary hydrocephalus is a pathological condition caused by the accumulation of cerebrospinal fluid (CSF), probably as a consequence of damage in its reabsorption mechanisms. It is a well-known complication of severe acquired brain injuries (sABIs), often diagnosed during inpatient rehabilitation [1,2,3]. The incidence of chronic secondary hydrocephalus is reported to range between 14 and 45%, and it is usually diagnosed between 3 and 12 months after brain injury [1,4,5,6,7].

Detecting secondary hydrocephalus in patients with sABIs is complex, due to their neurological impairment, difficulties in autonomously reporting symptoms and the actual lack of standardized methods of diagnosis. Moreover, even when a clear ventriculomegaly is found on CT or RMN scans, it is sometimes difficult to understand whether it is secondary to brain atrophy or the accumulation of CSF [1,2,5]. Hydrocephalus in patients with sABIs can present either with symptoms related to chronic hydrocephalus (cognitive impairment, gait disturbances and urinary incontinence) or with features more related to increased intracranial pressure (headache, papilledema, nausea, vomit and worsening of consciousness) [5,8]. In the absence of a gold standard for the diagnosis of secondary hydrocephalus, its recognition is often based on the combination of clinical observation and radiological findings. Subarachnoid and/or intraventricular hemorrhage, decompressive craniectomy, duration of coma, severity of brain injury (measured using the Glasgow Coma Scale score) and older age are reported as the main risk factors for hydrocephalus [4,6,9,10]. The main diagnostic criteria include a persistent disorder of consciousness, worsened or plateaued clinical recovery, elevated CSF pressure and/or clinical improvement in behavioral or motor capacities after high-volume lumbar puncture [3,11,12].

Given the difficulties in its diagnosis and treatment, the identification of hydrocephalus is important to clinicians dealing with the rehabilitation of patients with sABIs because it may delay or negatively affect their recovery. Moreover, being a treatable condition, early diagnosis and correct management are fundamental to identify patients who may be selected for surgical treatment, which is associated with a better outcome [2,4,6,10,11,13,14,15,16]. Surgical treatment usually consists in the placement of a ventriculoperitoneal shunt (VPS) or ventriculoatrial shunt (VAS) [13,14,15].

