### 2.5. Statistical Analysis Plan

Continuous variables will be presented as the mean and standard deviation or as the median and interquartile range. Normality in the distribution will be tested with the Shapiro–Wilk test. Categorical variables will be summarized in terms of absolute and relative frequencies.

To determine whether the new diagnostic protocol can improve the ability to detect hydrocephalus as well as the timeliness of the diagnosis and the clinical rehabilitative outcomes, the historical and prospective cohorts will be compared with respect to the following: hydrocephalus diagnosis detection rate, time from admission to diagnosis, LOS, incidence of clinical complications, and DRS and LCF scores at discharge (T3). In the subgroup of patients with low responsiveness, the clinical rehabilitative outcome at discharge will be measured using the CRS-R score. Continuous variables will be compared using Student’s *t* test, when normally distributed, or the Mann–Whitney U test otherwise. Categorical variables will be compared using Pearson’s χ^2^ test or Fisher’s exact test as appropriate. The same tests will be used to compare patients with and patients without a diagnosis of hydrocephalus belonging to the prospective cohort, in terms of the following: clinical rehabilitative outcome at T3 and T4 measured using the DRS, LCF and CRS-R scale scores; evolution from T0 to T4 of quality of life measured using the QOLIBRI-OS; neuroradiological characteristics at T1 and T3 or T4 measured using Evan’s index, callosal angle and volumetric analysis. To complement the information provided by the statistical tests, differences between groups will be quantified in terms of the effect size (standardized mean differences for continuous variables; difference between proportions or odds ratios for categorical variables) and its standard error. In addition, outcome variables will be compared between the historical and prospective cohorts, adjusting for demographic and clinical confounders in multivariable regression analyses. Confounders to be included in the models are those significantly associated with the outcomes and significantly different between the two cohorts. 

Two-sided tests will be carried out, and the statistical significance level will be set at 0.05. All analyses will be performed with Stata version 17.0 (Stata Corp., College Station, TX, USA).

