## 3. Expected Results

We expect to find, in the prospective cohort as compared to the historical cohort, an increase in the proportion of diagnosed cases, a significant reduction in the time elapsed between admission and diagnosis and, consequently, a shortened time to surgery as well as a shortened overall LOS.

We assume that early diagnosis and treatment may result in a decreased incidence of clinical complications and may improve the rehabilitative outcomes at discharge among patients with hydrocephalus, especially in the subgroup with low responsiveness.

In addition, we expect to obtain useful information about the diagnostic and prognostic value of the neuroradiological characteristics.

Lastly, from the comparison of patients with and without hydrocephalus in the prospective cohort, we expect to observe that the adoption of an objective and timely protocol for the diagnosis and treatment will allow patients with hydrocephalus to obtain similar clinical rehabilitative outcomes and perceived quality of life to those who do not develop this complication.

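### The comparison of patients with and without hydrocephalus is planned without adjustment, although the article's own risk factors for hydrocephalus make different prognoses in the two groups likely

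*Protocol article*

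**What the plan says.** Section 2.5 of the protocol article first sets out two-sample tests for the historical-versus-prospective comparison. Continuous variables get Student's t test "when normally distributed, or the Mann–Whitney U test otherwise"; categorical variables get a chi-square or Fisher test. It then carries these over: "The same tests will be used to compare patients with and patients without a diagnosis of hydrocephalus belonging to the prospective cohort". The outcomes are DRS, LCF and CRS-R at T3 and T4, the course of QOLIBRI-OS from T0 to T4, and imaging measures. It adds that "differences between groups will be quantified in terms of the effect size", with no adjustment mentioned.

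Adjustment comes next, for the other comparison only: "outcome variables will be compared between the historical and prospective cohorts, adjusting for demographic and clinical confounders in multivariable regression analyses". The rule for choosing covariates is tied to that comparison too: "Confounders to be included in the models are those significantly associated with the outcomes and significantly different between the two cohorts".

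The Introduction lists "Subarachnoid and/or intraventricular hemorrhage, decompressive craniectomy, duration of coma, severity of brain injury" and closes the list with "older age are reported as the main risk factors for hydrocephalus".

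Section 3 says what the within-cohort comparison should show: that the protocol "will allow patients with hydrocephalus to obtain similar clinical rehabilitative outcomes and perceived quality of life to those who do not develop this complication".

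**The concern.** The Introduction implies that patients who develop hydrocephalus will tend to be older and more severely injured, and more often to have had haemorrhage or craniectomy. If those features also slow recovery, the two groups have different expected DRS and LCF scores at discharge and at one year whatever hydrocephalus and its treatment do. A two-sample test cannot separate the two sources.

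What is at stake is the reading in Section 3. If the hydrocephalus group does worse, the shortfall may be case mix, and a useful pathway may look inadequate. If the groups look alike, that is also hard to interpret, because they did not start with the same prognosis.

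The article accepts the need to adjust for confounders between cohorts. It gives no reason for leaving adjustment out of the comparison where its own text makes imbalance predictable.

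**Working it through.** **1. The plan's own figures (Section 2.2).** Flow of 50–60 patients a year, two years, about 20% with hydrocephalus:
- 50 × 2 = 100 patients, of whom 0.20 × 100 = 20 with hydrocephalus (20 v 80).
- 60 × 2 = 120 patients, of whom 0.20 × 120 = 24 with hydrocephalus (24 v 96).

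This reproduces the stated 100–120 patients and at least 20 cases.

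**2. Precision of the unadjusted comparison, in SD units.** SE = √(1/n₁ + 1/n₂).
- 20 v 80: √(0.05 + 0.0125) = 0.25; 95% CI half-width 1.96 × 0.25 = 0.49.
- 24 v 96: √(0.0417 + 0.0104) = 0.228; half-width 0.45.

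**3. Reach of the stated adjustment.** The covariate rule selects variables that differ between the historical and prospective cohorts. A variable can be balanced between cohorts and still differ strongly between patients with and without hydrocephalus. The rule therefore does not cover this comparison.

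**4. Size of the distortion (illustration; the inputs are assumptions).** Take one standardised confounder that differs by d SD between the groups and correlates r with the outcome within groups. With no true hydrocephalus effect, the unadjusted difference is biased by b = d × r. The two-sided rejection rate at 0.05 is Φ(b/SE − 1.96) + Φ(−b/SE − 1.96). At 20 v 80:

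| Assumed d, r | Bias b (SD) | b/SE | Rejection, formula | Rejection, simulated t test |
|---|---|---|---|---|
| 0.3, 0.3 | 0.09 | 0.36 | 6.5% | 7% |
| 0.5, 0.5 | 0.25 | 1.00 | 17% | 16% |
| 0.8, 0.5 | 0.40 | 1.60 | 36% | 36% |

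The simulation used 4,000 runs per row. Linear regression on group plus the confounder, in the same runs, had bias of about 0 and rejected in about 5%. At 24 v 96 the formula gives 6.8%, 19.5% and 41.8%. A more extreme pair (0.8, 0.7) gives b = 0.56 and 61% at 20 v 80, but nothing in the article supports choosing it.

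**5. Cost in precision.** With a 20/80 split, imbalance of d multiplies the SE by √(1 + 0.16 d²). For d = 0.3 this is √1.0144 = 1.007; for d = 0.8 it is √1.1024 = 1.05. Outcome variance explained by the covariate offsets this: √(1 − r²) is 0.95 at r = 0.3 and 0.87 at r = 0.5.

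**The case against.** **The article is a condensed account, and a fuller plan may adjust.** This does not remove the point. Section 2.5 names the method for this comparison and gives adjustment to the other one. That is a stated choice.

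**The comparison is secondary.** The four aims in the Introduction rest on the historical comparison, where adjustment is planned. This stands and limits the weight of the point. Section 3 nevertheless draws a conclusion from the within-cohort comparison.

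**The factors are risk factors only.** A reader might infer that the article calls them causes of hydrocephalus, or says that they worsen outcome. It does neither. Their effect on DRS, LCF and quality of life is an assumption, though a modest one for severity and coma duration.

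**The bias may run against the authors.** A reader might infer that the unadjusted analysis would manufacture support for the protocol. With a worse case mix in the hydrocephalus group it would do the opposite and hide similarity. The rejection rates above count false differences, which would contradict the authors' expectation. What stands is that neither result can be interpreted as intended.

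**The size is not in the documents.** This is correct. A larger figure could be reached by adding separate effects of craniectomy, haemorrhage, age and GCS, but the sum is valid only if each effect is conditional on the others, and these factors plausibly overlap.

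**Data and numbers are limited.** Table 1 includes GCS but neither coma duration nor craniectomy, and Section 2.4 mentions only history-taking in general terms. About 20 cases, and fewer in the CRS-R subgroup, support only a few covariates.

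**Adjustment would not deliver the conclusion in Section 3.** Also correct. Within the cohort there is no comparison with patients managed without the protocol, and Section 2.4 confirms the diagnosis largely by improvement after the tap test on the same scales.

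**Conclusion.** The point holds in a limited form. Section 2.5 fixes unadjusted tests for a comparison whose groups are, on the article's own account, likely to differ in age and injury severity. Provided these factors also affect recovery, neither a difference nor a similarity at T3 or T4 can be attributed as Section 3 intends; the likely direction is against the expected similarity. With 20 v 80 patients, assumed confounding of 0.1–0.4 SD would raise the 5% error rate to about 7–36%. Those figures show scale only; the true bias cannot be derived from the article.

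The exposure is uneven. DRS and LCF at T3 and T4 are most affected. QOLIBRI-OS is analysed as change from T0 and is less so. The imaging comparison is a different matter, because imaging findings are part of how hydrocephalus is suspected.

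This should be changed, but it concerns a secondary comparison and leaves the planned historical-versus-prospective analysis untouched.

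**What to change.** In Section 2.5:
- For DRS and LCF at T3 and T4, and for QOLIBRI-OS change, add a linear or ordinal regression on hydrocephalus status.
- Fix a short covariate set in advance, chosen from the risk factors in the Introduction and not by significance. For example: age, one admission severity measure such as GCS, and haemorrhage or craniectomy if recorded.
- Allow at most one or two covariates in the CRS-R subgroup.
- Report the adjusted difference with its 95% CI alongside the two-sample tests.
- Leave the imaging comparisons as they are.

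In Section 3, state that similar outcomes in this comparison do not by themselves show an effect of the protocol.

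The cost is a little more analysis work, a check that the chosen covariates are recorded, and a small loss of precision from covariate imbalance (1–5% on the SE in the illustration), offset as far as the covariates explain outcome. Recruitment and care do not change.

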### 2.4. Clinical Diagnostic Protocol and Study Assessments

A multidisciplinary team of physiatrists, neuroradiologists, neuropsychologists and neurosurgeons designed the new protocol for the diagnosis of suspected secondary hydrocephalus and its confirmation, based on the best recommendations in the literature [18,19,20]. The timing and procedures included in the diagnostic protocol are shown in Figure 1. 

Within 7 days (week 1) of hospital admission, i.e., at baseline (T0), patients with sABIs will undergo the following evaluations:Socio-demographic and anamnestic data collection;Neurological examination;Clinical and functional assessment;Neuroradiological exam (brain CT);Neurophysiological exams.

Clinical and functional assessments will be performed at weeks 3 and 5, before the multidisciplinary team meeting. An additional CT scan and a brain MRI will be performed after 30 days (week 5) from admission (T1) to assess the presence of ventricular dilation signs. The first multidisciplinary team meeting will be held about 40 days (week 6) after admission, with the aim of evaluating the results of the neurological examination, neuroradiological exams, and clinical and functional assessments. The multidisciplinary team will identify patients with suspected hydrocephalus based on the presence of at least one of the following criteria:Neuroradiological criteria: increase in ventricular dimensions with supratentorial and subtentorial ventricular dilation, or both; sulcal reduction at the convexity; Evan’s index increase; callosal thickness reduction; callosal angle increase; presence of periventricular white matter changes; presence of aqueductal flow void.Clinical criteria: worsening or stopping of clinical recovery as assessed based on clinical scales and functional tests.

Patients with “suspected hydrocephalus” will undergo further evaluations to confirm the diagnosis, specifically:High-volume tap test (TT);CSF examination;Clinical and functional assessments 1, 3 and 7 days after TT;Multidisciplinary team evaluation 7 days after TT.

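### T1 imaging helps decide who is tapped and can be diagnosed, so the planned whole-cohort T1 comparison cannot by itself show diagnostic value

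*Protocol article*

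**What the plan says.** All places are in the protocol article.

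- **Section 2.4, timing.** CT and MRI are done at week 5 (T1). The multidisciplinary team reviews them at about week 6.
- **Section 2.4, suspicion.** "The multidisciplinary team will identify patients with suspected hydrocephalus based on the presence of at least one of the following criteria". The neuroradiological list includes ventricular enlargement and "Evan’s index increase; callosal thickness reduction; callosal angle increase". Worsening or arrested recovery is a separate clinical criterion, and it suffices alone.
- **Section 2.4, reference test.** Suspected patients "will undergo further evaluations to confirm the diagnosis", starting with the tap test. Confirmation requires an improvement afterwards in DRS, LCF, CRS-R or a functional test.
- **Section 2.5, analysis.** "The same tests will be used to compare patients with and patients without a diagnosis of hydrocephalus belonging to the prospective cohort", and one of the listed comparisons is "neuroradiological characteristics at T1 and T3 or T4 measured using Evan’s index, callosal angle and volumetric analysis". It is not restricted to tapped patients.
- **Section 3, interpretation.** "we expect to obtain useful information about the diagnostic and prognostic value of the neuroradiological characteristics". The Abstract says much the same.
- **Section 4.** One sentence can be read as saying that every sABI patient enters a protocol that includes a tap test. Section 2.4 limits the test to suspected patients.

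**The concern.** The measurement under study influences who receives the reference test, and patients who never receive it are counted as not having the condition. Patients with a large Evan's index increase are more likely to be suspected, therefore tapped, therefore diagnosed. Untapped patients fall into the undiagnosed group whatever their true state. Part of any T1 difference between the groups is then produced by the pathway.

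At stake is the claim about imaging. The study could report significant differences in Evan's index, callosal angle or ventricular volume as evidence of diagnostic value when these measures say nothing about tap-test response. Section 5 suggests that the protocol may inform guidelines on standardized neuroimaging, and neither limitation named in section 4 mentions this selection.

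**Working it through.** **1. The plan's own counts.** Section 2.2 gives 50–60 patients a year for two years, about 20% with hydrocephalus. 2 × 50 = 100 and 2 × 60 = 120; 0.20 × 100 = 20 and 0.20 × 120 = 24. The stated 100–120 patients and at least 20 cases reproduce. The check uses N = 110 and about 22 diagnosed.

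**2. Assumptions (not in the article).** The marker is standard normal and unrelated to tap response. The imaging value behind suspicion is positive in 30% of patients. Other routes to suspicion, independent of the marker, are positive in a share p_o from 0 to 80%. The analysed T1 value has correlation ρ with the value behind suspicion, from 1 down to 0.4. Values of ρ below 1 allow for the rule using increases while the analysis uses T1 measurements.

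**3. Expected spurious difference.**

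- Share tapped: p_s = 1 − (1 − 0.30)(1 − p_o).
- Response needed for 20% diagnosed: 0.20 / p_s.
- Cut-off for the top 30%: c = 0.524, with normal density φ(c) = 0.348.
- Marker mean in tapped, hence diagnosed, patients: ρ × 0.348 × (1 − p_o) / p_s.
- The overall mean is 0, so the difference between diagnosed and undiagnosed is that value divided by 0.80.

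For p_o = 0.30 and ρ = 1: p_s = 1 − 0.7 × 0.7 = 0.51; response 0.20 / 0.51 = 0.39; diagnosed mean 0.348 × 0.7 / 0.51 = 0.48; difference 0.48 / 0.80 = 0.60. The simulated standardised difference is 0.62, because the pooled SD is slightly below 1.

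**4. Simulation of the planned comparison** (3,000 runs per row, two-sided t test at 0.05, N = 110):

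| Other routes | Share tapped | SMD, ρ = 1 | AUC, ρ = 1 | False-positive rate, ρ = 1 | ρ = 0.7 | ρ = 0.4 |
|---|---|---|---|---|---|---|
| 0% | 0.30 | 1.79 | 0.94 | 1.00 | 1.00 | 0.69 |
| 10% | 0.37 | 1.18 | 0.82 | 0.99 | 0.88 | 0.43 |
| 30% | 0.51 | 0.62 | 0.68 | 0.70 | 0.42 | 0.17 |
| 50% | 0.65 | 0.35 | 0.60 | 0.31 | 0.16 | 0.09 |
| 80% | 0.86 | 0.11 | 0.53 | 0.07 | 0.06 | 0.06 |

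Repeat runs, including the Mann–Whitney test, gave up to 0.74 in the 30% row and up to 0.08 in the 80% row (ρ = 1). At N = 100 and N = 120 the 30% row gives 0.67 and 0.74. If every patient were tapped, the rate is 0.046–0.059.

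**5. Tapped patients only, confirmed against not confirmed.** If response does not depend on route, the rate is nominal (0.046–0.059). That condition matters. Suppose instead that imaging flags 30%, the clinical route flags 25%, and response is 60% if clinically flagged and 25% otherwise. The marker mean is 0.348 / 0.30 = 1.16 in imaging-positive patients and −0.348 / 0.70 = −0.50 in the rest.

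- Shares of the cohort: both routes 0.075, imaging only 0.225, clinical only 0.175.
- Confirmed: imaging-positive 0.6 × 0.075 + 0.25 × 0.225 = 0.101; clinical only 0.6 × 0.175 = 0.105. Mean (0.101 × 1.16 − 0.105 × 0.50) / 0.206 = 0.31.
- Not confirmed: imaging-positive 0.4 × 0.075 + 0.75 × 0.225 = 0.199; clinical only 0.4 × 0.175 = 0.070. Mean (0.199 × 1.16 − 0.070 × 0.50) / 0.269 = 0.73.
- Difference 0.31 − 0.73 = −0.42. Simulation gives an SMD of about −0.43 to −0.44 and a false-positive rate of 0.30–0.32.

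Here a useless marker looks anti-diagnostic. Within a single route, response in this model is unrelated to the marker and the distortion disappears.

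**The case against.** **The comparison is not called an accuracy analysis.** Section 2.5 plans no sensitivity, specificity or AUC, and none of the four aims in the Introduction rests on this contrast. That is correct and limits the consequence to the imaging claim. But section 2.5 does plan significance tests and effect sizes, the Abstract and section 3 expect diagnostic value, and the article describes no other analysis of that value.

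**Imaging is only one route.** Clinical criteria suffice alone, seven imaging signs are joined by an at-least-one rule, the rule uses increases while the analysis uses T1 values, and volumetric analysis is not itself a named criterion. The team can also raise suspicion later in the stay. All of this stands and weakens the bias. A reader might infer that a useless marker is bound to look diagnostic; the article does not support that, because with most patients tapped the error rate is close to nominal. On the other side, the other imaging signs come from the same scans and may correlate with the marker, which would make the dilution smaller than modelled.

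**Incorporation bias.** A reader might infer that imaging is part of the diagnosis itself. No imaging item appears among the confirming changes in section 2.4, so the supportable label is partial verification.

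**Undiagnosed patients mostly untapped.** A reader might infer this too, but the article gives no share tapped.

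**Section 4 may mean that all patients are tapped.** The bias would then vanish. Section 2.4 sets out the operative steps and restricts the test to suspected patients; the two need reconciling.

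**Conclusion.** The point holds as partial-verification bias in the T1 imaging comparison. The direction follows from the article's own pathway; the size does not, because the share tapped and the link between each marker and the suspicion rule are unstated. For a useless marker with about 110 patients and 22 diagnosed, the false-positive rate runs from near nominal (86% tapped), through about 0.4 to 0.7 (51% tapped, correlation 0.7 to 1), to 0.99 when imaging is almost the only route. At a correlation of 0.4 it is lower throughout: 0.17 at 51% tapped.

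It is also tempting to treat a tapped-only analysis as unbiased. It is so only if response does not vary by route to suspicion, which the article gives no reason to assume. The cohort-versus-historical comparisons that serve the four aims are not affected by this point.

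**What to change.** - **Section 2.5, whole cohort.** Label the T1 comparison of diagnosed and undiagnosed patients as descriptive, and state that it is not evidence of diagnostic value.
- **Section 2.5, diagnostic statements.** Base these on tapped patients. Compare the scan that preceded the tap test between confirmed and not-confirmed patients, and report AUC with 95% CI. Stratify by, or adjust for, route to suspicion (imaging, clinical, both).
- **Data recording.** Record the route for each suspected patient when the team meets.
- **Abstract and section 3.** Limit the claim to association with tap-test response among suspected patients.
- **Sections 2.4 and 4.** Reconcile the statements on who has the tap test.

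**Cost.** Wording and analysis changes, plus a record of the route; no new examinations. The comparison is smaller, with about 20–24 confirmed cases against the tapped non-responders, so intervals widen. Splitting those cases over three routes leaves few in each, so adjustment may be more workable than separate AUCs. Results will apply only to suspected patients.

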### 2.2. Feasibility 

Patients with sABIs of different etiologies (traumatic, vascular, anoxic, infectious, neoplastic, etc.) will be recruited from those hospitalized in the Severe Acquired Brain Injury Unit or in the Intensive Care Unit (ICU), depending on their clinical conditions. The presence of an ICU in our rehabilitation institute ensures prompt treatment soon after the acute brain injury event, through the implementation of a personalized rehabilitation project in the early stage.

The recruitment of the prospective cohort will last two years. The expected annual flow of patients with sABIs is 50–60, and the expected proportion with hydrocephalus is about 20%, leading to a total number of 100–120 patients with sABIs and at least 20 patients with a confirmed diagnosis of hydrocephalus.

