Some patients with sABIs present with prolonged disorders of consciousness (unresponsive wakefulness syndrome or minimal conscious state). Arnts and colleagues [19] discussed both the difficulties in the diagnosis and the dilemmas in the treatment of CSF disorders in patients with prolonged disorders of consciousness and reviewed evidence from the literature to implement an active surveillance protocol for the detection of this late but treatable complication. Moreover, they advocated a low threshold for cerebrospinal fluid diversion when hydrocephalus is suspected, even months or years after brain injury. In addition, an accurate and structured diagnostic investigation with CT and MRI allows the identification of patients clinically not suspected of hydrocephalus. 

It is generally recognized that a multidisciplinary approach plays an important role in the management and treatment of suspected hydrocephalus cases, because risks and benefits should be carefully considered and calibrated on the patient [1,7]. In our protocol, the multidisciplinary team represents the most important feature since the exchange of views among experts allows for evaluating patients’ conditions in deeper detail and identifying the best care pathway.

This new clinical diagnostic protocol has been designed to integrate all the aforementioned ingredients. 

One important limitation is that the new protocol has already been adopted by our institution; thus, carrying out a randomized clinical trial to assess its efficacy is not feasible for ethical reasons. The second limitation is that the historical cohort may not include complete information on the variables of interest. 

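### Choosing confounders by two significance tests leaves small imbalances unadjusted in the historical-versus-prospective comparison; a short covariate list should be fixed in advance

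*Protocol article*

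**What the plan says.** Section 2.5 of the protocol article first compares the cohorts with unadjusted tests and effect sizes. It then adds that "outcome variables will be compared between the historical and prospective cohorts, adjusting for demographic and clinical confounders in multivariable regression analyses". Entry to those models is governed by one sentence: "Confounders to be included in the models are those significantly associated with the outcomes and significantly different between the two cohorts". The only threshold given is in the same section: "Two-sided tests will be carried out, and the statistical significance level will be set at 0.05". No covariate is named as always included.

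Section 1 already lists known risk factors: subarachnoid or intraventricular haemorrhage, decompressive craniectomy and coma duration, together with "severity of brain injury (measured using the Glasgow Coma Scale score) and older age are reported as the main risk factors for hydrocephalus". Section 4 explains why there is no concurrent randomised control: "carrying out a randomized clinical trial to assess its efficacy is not feasible for ethical reasons".

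On size, section 2.2 says "The recruitment of the prospective cohort will last two years" and "The expected annual flow of patients with sABIs is 50–60, and the expected proportion with hydrocephalus is about 20" per cent, "leading to a total number of 100–120 patients with sABIs and at least 20 patients with a confirmed diagnosis of hydrocephalus". The size of the historical cohort (2015-2019) is not stated.

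**The concern.** The bias from leaving out a covariate is roughly its imbalance between cohorts multiplied by its association with the outcome. A p-value measures neither factor on its own, because it also depends on sample size. A double significance filter therefore tends to leave out covariates with small imbalances. Several of these, acting together, can shift the estimated effect of the new diagnostic protocol. The smaller the comparison, the larger the imbalance that goes unadjusted.

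This matters because the control group is historical and the regression is the only covariate adjustment the article describes. The rule is a stated method, so it cannot be treated as a detail left to a fuller analysis plan.

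**Working it through.** **The plan's own figure.** 2 years × 50-60 per year = 100-120 patients; 20% of these = 20-24 with hydrocephalus. The stated figures reproduce.

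**Assumptions.** The article does not give these inputs.
- Historical cohort: 5 years × 50-60 = 250-300. The midpoints are 275 historical and 110 prospective. A sensitivity value of 621 is the size of the earlier study cited in section 1.
- Historical hydrocephalus cases: 13.2% × 250-300 = 33-40.
- Five independent confounders, each imbalanced by d SD, each with slope 0.3 per SD. Outcome residual SD is 1 and the true cohort effect is zero.

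**Step 1: chance of passing the between-cohort test.** The standard error of a standardised difference is s = √(1/275 + 1/110) = 0.1128. At d = 0.2, d/s = 1.77, and P(Z > 1.96 − 1.77) is about 43%. The same formula gives:

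| Patients | d = 0.1 | 0.2 | 0.3 | 0.4 |
|---|---|---|---|---|
| 250 vs 100 | 13% | 39% | 72% | 92% |
| 275 vs 110 | 14% | 43% | 76% | 94% |
| 300 vs 120 | 15% | 46% | 79% | 96% |
| 621 vs 120 | 17% | 52% | 85% | 98% |

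The outcome test adds little here. The covariate-outcome correlation is about 0.3/√(1 + 5 × 0.09) = 0.25, which with 385 patients gives t of about 5.

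**Step 2: bias left by the rule.** Crude bias is 5 × 0.3 × d. A covariate is dropped when its observed difference D lies within ±c, where c = 1.96 × 0.1128 = 0.2211. The part left per confounder is 0.3 × E[D; |D| < c]. This expectation equals d·P − s·[φ(b) − φ(a)], with b = (c − d)/s, a = (−c − d)/s and P the chance of being dropped. At d = 0.2 it is 0.2 × 0.574 − 0.1128 × (0.392 − 0.0004) = 0.0706. Multiplying by 5 × 0.3 gives 0.106, against 0.111 by simulation.

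**Step 3: type I error.** Simulation of the two-test rule at 275 vs 110, with all imbalances in the same direction:

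| d | Crude bias | Bias left | Type I error |
|---|---|---|---|
| 0.1 | 0.15 | 0.09 | 10.9% |
| 0.2 | 0.30 | 0.11 | 12.7% |
| 0.3 | 0.45 | 0.06 | 8.0% |
| 0.4 | 0.60 | 0.02 | 5.0% |

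With the directions drawn at random, type I error under the rule was 5.0-6.0%. With all five covariates kept regardless of p-value it was 4.2-6.0%. Other cohort sizes agree: at d = 0.2 in the same direction, the rule gave 13.1% (250 vs 100) and 11.5% (300 vs 120), against 5.0% and 3.7% with a fixed set. A single confounder at d = 0.2 (250 vs 100) gave only 6.4%, against 5.8%.

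**Step 4: outcomes that exist only in diagnosed patients.** With 33 vs 20 cases, s = √(1/33 + 1/20) = 0.283. The chance of passing the between-cohort test is 18% at d = 0.3 and 42% at d = 0.5. With both tests and three confounders at d = 0.3, simulation dropped true confounders 87-89% of the time (33 vs 20 and 40 vs 24). The bias left was about 0.17 and type I error 7.0-8.9%.

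**The case against.** Selection by significance is common, and here it works in part. At d = 0.2 it cuts the crude bias from about 0.30 to 0.11, and at d = 0.3 from about 0.45 to 0.06. The imbalances that would do most damage are the ones it catches most reliably. The article also takes other precautions: it leaves out 2020-2021 to avoid pandemic-related selection, reports effect sizes, and acknowledges the lack of randomisation and possible gaps in historical data. All of this stands.

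A reader might go further and infer four things that the documents do not support.
- That moderate imbalances usually escape adjustment. In the full cohorts, about 75% of covariates are kept at 0.3 SD and 94% at 0.4 SD. Only small imbalances usually escape.
- That the 5% error rate is certainly wrong. Clear inflation needs several small imbalances pushing the same way, and the article gives neither sizes nor directions.
- That the regression is the only safeguard of any kind. It is the only covariate adjustment described, which is a narrower statement.
- That one long forced list would suit every outcome. About 20 prospective and 33-40 assumed historical cases cannot carry it. The interval from injury to admission, an obvious candidate, is not named among the article's variables.

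None of this makes the two-test rule a sound way to decide what is a confounder.

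**Conclusion.** The point holds in a limited form. The rule leaves small imbalances (about 0.1-0.2 SD in the full cohorts) mostly unadjusted, and larger ones among diagnosed patients. In the assumed full-cohort scenarios the residual bias is about 0.02-0.11 residual-SD units. Type I error is about 5-13% if the imbalances align and near 5% if they offset. The mechanism is certain. The size is not, because it rests on an assumed historical sample size, imbalances, slopes and number of confounders, and on a linear outcome model. This is a should-fix: a better method is available at small cost, but the planned adjustment is weakened rather than void.

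**What to change.** Replace the selection sentence in section 2.5 with a short covariate list, fixed before the historical data are extracted and kept whatever the p-values:
- age, GCS, subarachnoid or intraventricular haemorrhage, decompressive craniectomy and coma duration, all from section 1;
- aetiology;
- the T0 value of the scale being analysed, where the historical records hold it.

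For the detection rate, and for outcomes defined only in diagnosed patients such as time from admission to diagnosis, specify a shorter list, propensity weighting or penalised regression. Keep the two-test model only as a sensitivity analysis.

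The cost is about one paragraph of text, some degrees of freedom, and extraction of these variables for the historical cohort. A method for missing historical values must also be stated, since section 4 warns that those data may be incomplete.
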